## Study aims

### Overall aim

To assess the physical and insecticidal durability of an alpha-cypermerthrin and PBO ITN (DuraNet® Plus®) compared to a standard alphacypermethrin only net (DuraNet®) over 3 years of operational use in communities in Benin, Cameroon and Tanzania.

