### Bioefficacy studies and chemical analysis

A separate subsample of nets belonging to cohort 2 will be randomly selected per arm for bioefficacy studies and chemical analysis. Nets of each type (DuraNet® Plus and DuraNet®) will be destructively sampled from households at 6, 12, 18-, 24-, 30- and 36-months post-distribution and replaced with new nets of the same type (brand) at each sampling point. They will be subjected to chemical analysis to monitor alphacypermethrin and PBO content and to laboratory bioassays (WHO cone bioassays and tunnel tests where necessary) and experimental hut trials to monitor entomological efficacy against mosquito vectors over time. For laboratory bioassays, net pieces measuring 30cmx30cm will be cut from each net following WHO guidelines [9]. The number of whole ITNs of each type to be subjected to each type of study at each timepoint is summarised in Table 2 below.

**Table 2 Tab2:** Number of DuraNet® Plus and DuraNet® ITNs to be sampled for laboratory assays, chemical analysis and hut trials at each study site

Months post ITN distribution	No of ITNs for Laboratory assays	No. of pieces per ITN	Total number of pieces for bioassays	No. of pieces for chemical analysis^a^	ITNs for hut trials^b^
0	30	5	150	150	-
6	30	4	120	-	-
12	30	4	120	120	54
18	30	4	120	-	-
24	30	4	120	120	54
30	30	4	120	-	-
36	50	4	200	200	54
**Total**	**230**		**950**	**590**	**162**

^a^ Net piece preserved for chemical analysis will be obtained from adjacent positions on the same ITNs cut for bioassays. These net pieces would measure 30cmX30cm

^b^The hut trials will be performed only in Benin but will include nets from all study sites

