#### WHO cone bioassays and tunnel tests

Cone bioassays and tunnel tests will be performed at research partner institutions in each study country (Centre de Recherche Entomologique de Cotonou in Benin, Centre for Research in Infectious Diseases, Cameroon, and Vector Control Training Centre in Tanzania). To monitor the bioefficacy of alphacypermethrin in DuraNet® Plus and DuraNet®, ITN pieces obtained from each field collected net will be tested in standard WHO cone bioassays. One hundred (100) unfed 3–5 days old mosquitoes of the susceptible *Anopheles gambiae* Kisumu strain will be exposed for 3 min to each ITN in replicates of 5 mosquitoes per cone and 2 cones per net piece. Knockdown will be recorded after 60 min and mortality rates after 24 h. Comparison will be made to a new unused net of each ITN type. ITNs which fail to achieve WHO efficacy criteria in cone bioassays (pooled knock-down is ≥ 95% and/or pooled 24 h mortality is ≥ 80%) will be subjected to tunnel tests. For tunnel tests, 100 unfed 5–8 days old susceptible Kisumu mosquitoes will be exposed overnight to one ITN piece from each failed net and mortality (after 24 h) and blood-feeding inhibition rates measured following standard WHO protocols. The proportion of ITNs of each type passing criteria for alpha-cypermethrin bioefficacy in cone bioassays (≥ 95% knockdown or ≥ 80% mortality) and/or tunnel tests (≥ 80% mortality or ≥ 90% blood-feeding inhibition) will be determined for each study site. All cone bioassays will be performed at 27 ± 2 °C and 75% ± 10%

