To monitor the bioefficacy of PBO in DuraNet® Plus, tunnel tests will be performed using 1 net piece from ITNs withdrawn for bioassays at 12, 24 and 36 months using the pyrethroid resistant *An. coluzzi* Akron strain (BEI resources) for Benin and Cameroon and the pyrethroid resistant *An gambiae ss* Zenet strain in Tanzania. Both strains exhibit intense resistance to pyrethroids mediated by high kdr frequencies and overexpressed P450 enzymes evidenced by increased mortality with alpha-cypermethrin following PBO pre-exposure in susceptibility bioassays. They will be fully characterised prior to each round of laboratory bioassays. The proportion of DuraNet® Plus ITNs inducing ≥ 80% mortality of the pyrethroid resistant strain in tunnel tests will also be determined for each study site. Comparison will be made with a new unused DuraNet® Plus at each timepoint. All tunnel tests will run overnight between 18:00 and 09:00 at 27 ± 2 °C and 75% ± 10% relative humidity.

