### Data management and analysis

Household data collected during the census and ITN follow up surveys will be captured on electronic forms using smartphones installed with OpenDataKit (ODK) Collect in Benin and by paper forms in Cameroon and Tanzania. Data from the surveys at 12, 24, and 36 months will be used to calculate attrition, functional survival and median survival time using Kaplan–Meier estimators. For functional survival, nets reported as given away, sold, or stolen will be excluded from the analysis. Negative binomial regression will be used to compare hole surface area between DuraNet® Plus and DuraNet®. Data on WHO bioassays and tunnel tests will be obtained from 30 nets of each product type sampled at each time point. A chi-squared test will be used to assess the proportion of nets of each ITN type passing the WHO criteria for alphacypermethrin and PBO bioefficacy based on combined cone and tunnel tests. Proportional outcomes (mortality, blood-feeding, exophily) from the experimental hut trials will be compared at each time point using mixed effects logistic regression, with huts, sleepers, net replicate and nightly observational error included as random-effects while numerical outcomes (entry) will be compared with negative binomial regression. A separate model will be fitted for each outcome to determine whether there is a significant change in improved mosquito mortality achieved DuraNet® Plus compared to DuraNet® over time and between the three countries. All analysis will be performed on STATA version 17.

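### The alpha-cypermethrin bioassay comparison is a plain chi-squared test, apparently on 30 v 30 nets by country; a country-stratified test would use the 90 v 90 planned nets (150 v 150 at 36 months)

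*Protocol article*

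**What the plan says.** All references are to the protocol article.

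- **Test.** Data management and analysis: "A chi-squared test will be used to assess the proportion of nets of each ITN type passing the WHO criteria". No country stratum, country term or pooling rule is attached to it.
- **Number of nets.** The sentence before it: "Data on WHO bioassays and tunnel tests will be obtained from 30 nets of each product type sampled at each time point". It does not say whether this is per site or overall.
- **Table 2** (Bioefficacy studies and chemical analysis) settles the level. Its caption reads "Number of DuraNet® Plus and DuraNet® ITNs to be sampled for laboratory assays, chemical analysis and hut trials at each study site". The table has 30 nets at 0 to 30 months and, in its last row, "36 50 4 200 200 54", which is 50 nets at 36 months.
- **Reporting level.** WHO cone bioassays and tunnel tests: the proportion of nets of each type meeting the alpha-cypermethrin criteria "will be determined for each study site".
- **Aim.** The overall aim compares the two products "over 3 years of operational use in communities in Benin, Cameroon and Tanzania".
- **Randomisation.** Households are the unit, with 920 per arm at each site (Randomisation, blinding and sample size calculations).

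**The concern.** Read together, these sections describe a comparison of 30 with 30 nets inside one country, made separately in three countries, with no combined estimate. The alpha-cypermethrin assay has what is needed to combine: two common products, one named susceptible strain, one pass rule, and arms randomised at every site. Each country therefore gives its own randomised contrast, and stratifying by country combines the three without mixing country differences into the product comparison.

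At stake is how a non-significant result will be read. A site-level finding of no difference on 30 v 30 nets is weak evidence that the two nets keep their pyrethroid activity equally well, and the article intends its results to inform procurement.

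The other possible reading is one chi-squared test on the nets of all three countries together. That uses all the nets but ignores country, although the Discussion itself expects durability to vary between communities.

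**Working it through.** **Inputs from the article.** 30 nets per product per site at 6, 12, 18, 24 and 30 months and 50 at 36 months (Table 2); three sites; equal numbers per product. Hence 3 × 30 = 90 per product, and 3 × 50 = 150 at 36 months.

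**Assumptions.** Two-sided 5% level; nets independent; the pass rates below. The article gives no pass rate, effect size or power for this outcome, so there is no figure of its own to reproduce.

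**Formula (normal approximation).** Power = Φ[(d − 1.96·s0)/s1], where d is the difference in pass rates, s0 = √(2·p̄(1 − p̄)/n) and s1 = √((p1(1 − p1) + p2(1 − p2))/n).

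80% v 60%, so p̄ = 0.70:
- n = 30: s0 = 0.1183, s1 = 0.1155; (0.20 − 0.2319)/0.1155 = −0.28; power 0.39.
- n = 90: s0 = 0.0683, s1 = 0.0667; (0.20 − 0.1339)/0.0667 = 0.99; power 0.84.

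**Exact and simulated power.** The single-site columns enumerate both binomials for the uncorrected chi-squared test. The stratified columns simulate a Cochran-Mantel-Haenszel test over three countries with equal pass rates: [Σ(X − m/2)]² / Σ[n²m(2n − m)/((2n)²(2n − 1))], compared with 3.841. Here X is the number of passes for one product in a country and m the passes for both.

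| Assumed pass rates | One site, 30 v 30 | Stratified, 3 × 30 v 30 | One site, 50 v 50 | Stratified, 3 × 50 v 50 |
|---|---|---|---|---|
| 90% v 80% | 0.19 | 0.47 | 0.30 | 0.68 |
| 80% v 60% | 0.39 | 0.84 | 0.60 | 0.97 |
| 90% v 70% | 0.50 | 0.93 | 0.73 | 0.99 |
| 90% v 60% | 0.80 | 1.00* | 0.95 | 1.00* |
| 90% v 50% | 0.95 | 1.00* | 1.00 | 1.00* |

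*Exact power of a single 90 v 90 or 150 v 150 test; the two approaches agree closely when countries have equal pass rates.

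**Ratios, site to stratified.** At 6 to 30 months: 0.19/0.47 = 0.40, 0.39/0.84 = 0.46, 0.50/0.93 = 0.54, rising to 0.80 for 90% v 60%. At 36 months: 0.30/0.68 = 0.44, 0.60/0.97 = 0.62, 0.73/0.99 = 0.74.

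**Difference detectable with 80% power from a 90% pass rate.** 31 points at n = 30 against 16 at n = 90; 23 points at n = 50 against 12 at n = 150.

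**Precision.** With similar countries the standard error of the common difference is 1 − 1/√3 = 42% smaller than that of one site.

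**If the test is pooled and ignores country.** Both tests were simulated on the same data (200,000 trials, 30 v 30 per country). With pass rates of 95%, 90%, 85% v 85%, 75%, 65%, the stratified test has power 0.78 and the pooled test 0.77. With more spread between countries (95%, 80%, 50% v 85%, 60%, 30%), it is 0.76 against 0.68. The loss from pooling is small unless countries differ markedly.

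**The case against.** **The article does not say that the test is run by site.** This stands. Determining a proportion per site is a reporting level, and the analysis section does not exclude a combined test. A reader might infer a fixed plan of 18 separate tests (three sites by six field time points); the text does not support that as a statement of fact. By-site testing is the more natural reading only because the analysis section gives 30 nets, which is Table 2's per-site count.

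**How countries are combined may be left to an analysis plan not shown.** Partly right. An article need not give that detail, and a Cochran-Mantel-Haenszel test is itself a chi-squared test. But the article does fix a test and a number of nets, and the same paragraph plans a between-country comparison for the hut trials and none here.

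**The trial is sized per site and durability is local.** True, and a reason to keep the site results. It does not argue against a stratified summary beside them.

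**Large differences may not be expected.** The nets carry similar alpha-cypermethrin (6.0 and 5.8 g/kg), and nets failing the cone test go on to a tunnel test. This is fair, and the assumed pass rates are illustrative. If true differences are small, though, by-site testing is weaker still.

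**Multiplicity remains.** One stratified test at each of six time points is still six tests. The case here rests on power and precision, not on false positives.

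**Conclusion.** The point holds as an improvement to a stated analysis. On the by-site reading, power at 6 to 30 months is roughly 40% to 54% of what the planned nets would give for the assumed differences of 10 to 20 points. At 36 months, the end of the three-year aim, the loss is smaller for the 20-point differences (0.60 v 0.97 for 80% v 60%). On the pooled reading the cost is a design factor left out, with a modest loss of power when countries differ. Stratifying by country improves on either.

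A reader might go further in four ways that the documents do not support:
- That power is halved throughout. The size depends on assumed pass rates, and for 90% v 60% a single site already has power 0.80 with 30 v 30.
- That 90 v 90 nets are already in hand. The Status of study section reports only the 6-month bioassays as complete; later counts are planned.
- That the same applies to PBO bioefficacy. The article says "To monitor the bioefficacy of PBO in DuraNet® Plus, tunnel tests will be performed using 1 net piece from ITNs withdrawn for bioassays": DuraNet Plus alone, with different resistant strains by country, so there is no common two-product contrast to stratify.
- That functional survival needs the same change. It is sized separately at each site, and nothing calculated here bears on it.

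One textual conflict stands whatever the reading: the analysis section gives 30 nets at each time point, while Table 2 gives 50 at 36 months.

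**What to change.** In Data management and analysis, for alpha-cypermethrin bioefficacy only:

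1. Replace the chi-squared wording with a Cochran-Mantel-Haenszel test of DuraNet Plus against DuraNet at each time point, stratified by country.
2. Report a country-stratified common risk difference with its 95% CI.
3. Show the site-specific pass proportions and a test of heterogeneity between countries beside it.
4. Reconcile the stated 30 nets per time point with Table 2, and say that the counts are per site.

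No extra nets or assays are needed. The downside is that a common effect is summarised across countries that may differ, and with three small strata a heterogeneity test has limited power. The site results therefore need to be read with the summary, not replaced by it.

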**Methods:**

The study will be conducted in parallel in selected villages in Zakpota District in Benin, Mbalmayo, District in Cameroon and Muheza District in Tanzania. In each country, ~ 1800 households will be recruited and randomised to receive DuraNet® Plus or DuraNet® (a WHO prequalified alphacypermethrin-only ITN). Follow up surveys will be performed at 1 month post distribution to investigate adverse events and subsequently every 6–12 months to assess ITN attrition and fabric integrity following standard WHO procedures. A second cohort of nets will be withdrawn every 6–12 months and assessed for alpha-cypermethrin and PBO content and for entomological activity in laboratory bioassays (cone bioassays and tunnel tests). Alpha-cypermethrin bioefficacy will be monitored using the susceptible Anopheles gambiae Kisumu strain in cone bioassays while PBO bioefficacy will be monitored using pyrethroid resistant strains with overexpressed P450 enzymes in tunnel tests to determine the proportion of efficacious nets (≥ 95% knockdown, ≥ 80% mortality or ≥ 90% blood feeding inhibition in tunnels) at each time point. Nets withdrawn at 12, 24 and 36 months from each country will also be tested in experimental hut trials against wild free-flying pyrethroid resistant Anopheles gambiae sl in Côvè Benin to investigate the superiority of DuraNet® Plus over DuraNet® at each time point under semi field conditions.

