## Discussion

This protocol describes a large-scale study to evaluate the durability of DuraNet® Plus, a new WHO prequalified alphacypermethrin-PBO net compared to an alphacypermethrin-only net (DuraNet®) in communities in 3 different countries across sub-Saharan Africa. While all WHO prequalified pyrethroid-PBO ITNs have at least demonstrated improved entomological efficacy compared to pyrethroid-only nets, their impact under operational conditions will largely depend on their durability and quality. ITN durability studies are useful for planning the replacement of worn-out nets and making programmatic and procurement decisions [10]. Durability can however be influenced by several factors including location specific effects such washing practices, net care, housing structure, climate etc. which can result in significant variations in ITN retention and impact from one community to another [13]. The multi-country approach of our study takes this into account and will provide useful information about how these factors would affect the physical durability of a pyrethroid-PBO net across communities in countries in the three major malaria endemic regions of sub-Saharan Africa.

In addition to their physical durability, novel ITNs with new active ingredients other than pyrethroids, need to be closely monitored for the durability of their bioefficacy under field use. Earlier studies investigating the durability of Olyset® Plus nets (a permethrin-PBO net) in line with existing WHO guidelines, used only pyrethroid-susceptible mosquitoes for monitoring their bioefficacy [16]. However, this approach would likely lead to unreliable results as the impact of PBO will be confounded by the pyrethroid insecticide in the net to which the mosquitoes are susceptible. Effective monitoring of the biological activity of the PBO component in these nets requires a pyrethroid-resistant strain with evidence of metabolic resistance mechanisms as proposed in our study protocol and in recently developed consensus standard operating procedures [17]. This allows for measurement of the additional biological effect of PBO in the net over the pyrethroid. Recognising that mosquito strains used in laboratory bioassays are prone to variability in their insecticide resistance profiles over time, to improve comparability of bioefficacy data across our study sites, we will characterise the strains used in our study prior to each round of bioassays following consensus protocols [18].

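### The laboratory PBO endpoint is stated inconsistently across the article and, as defined, measures whole-product activity rather than the added effect of PBO

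*Protocol article*

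**What the plan says.** All references are to the protocol article.

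- **Abstract, Methods.** One sentence covers the susceptible-strain cone test and the resistant-strain tunnel test. It ends with a single list of criteria: "to determine the proportion of efficacious nets (≥ 95% knockdown, ≥ 80% mortality or ≥ 90% blood feeding inhibition in tunnels".
- **WHO cone bioassays and tunnel tests, alpha-cypermethrin.** Both net types are tested with the susceptible strain: "To monitor the bioefficacy of alphacypermethrin in DuraNet® Plus and DuraNet®, ITN pieces obtained from each field collected net will be tested". Nets that fail the cone test go on to a tunnel test, and the pass rule is explicit: "≥ 95% knockdown or ≥ 80% mortality) and/or tunnel tests (≥ 80% mortality or ≥ 90% blood-feeding inhibition".
- **WHO cone bioassays and tunnel tests, PBO.** One piece per net is run in a tunnel with a resistant strain at 12, 24 and 36 months. The outcome is "The proportion of DuraNet® Plus ITNs inducing ≥ 80% mortality of the pyrethroid resistant strain in tunnel tests", and the reference is a new DuraNet Plus.
- **Data management and analysis.** The chi-squared test concerns "the proportion of nets of each ITN type passing the WHO criteria for alphacypermethrin and PBO bioefficacy based on combined cone and tunnel tests".
- **Discussion.** PBO activity is to be assessed straight in tunnels with a resistant strain. Of this approach the text says: "This allows for measurement of the additional biological effect of PBO in the net over the pyrethroid".

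**The concern.** Adapting the WHO method to assess PBO is the modification that the Background announces, and the Conclusion offers the methods as a basis for new guidelines. The laboratory PBO endpoint therefore needs one definition and a claim that its comparator supports.

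Two things are at stake. A net that falls short on mortality but reaches 90% feeding inhibition fails under the bioassay section and can pass under the abstract's list. If this stays open, the rule can be chosen after the results are seen. Second, a falling pass rate in aged DuraNet Plus could reflect loss of alpha-cypermethrin, of PBO, or of both, yet the Discussion presents the assay as measuring PBO's added effect.

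**Working it through.** The article gives no figure for this endpoint to reproduce, so the check is a side-by-side reading followed by an illustration of size.

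**Step 1. The statements compared**

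| Place | Assay | Pass rule | Net types and reference |
|---|---|---|---|
| Abstract | Both assays in one sentence | Knockdown, mortality or feeding inhibition | Not separated |
| Bioassay section, alpha-cypermethrin | Susceptible strain; cone, then tunnel for failures | Cone: ≥95% knockdown or ≥80% mortality. Tunnel: ≥80% mortality or ≥90% inhibition | Both types, each against a new net of its type |
| Bioassay section, PBO | Resistant strain; tunnel only | ≥80% mortality | DuraNet Plus against new DuraNet Plus |
| Data management and analysis | Combined cone and tunnel | WHO criteria, no threshold given | Each type |
| Discussion | Resistant strain; tunnel only | None stated | DuraNet Plus |

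This shows three mismatches for PBO:
- Threshold: the abstract against the bioassay section.
- Assay basis: combined cone and tunnel against tunnel only.
- Net types: each type against DuraNet Plus alone.

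**Step 2. Nets concerned.** Table 2 gives 30 + 30 + 50 = 110 nets per type per site at 12, 24 and 36 months. The analysis section's 30 at every time point would give 90. Either way, the article defines no PBO outcome or reference for the DuraNet nets.

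**Step 3. What the assay can show.** Let M(a, b) be resistant-strain mortality on a net with alpha-cypermethrin activity a and PBO activity b, at time t or new (time 0).
- Planned contrast: M(a_t, b_t) − M(a_0, b_0). It can fall if either a or b falls.
- PBO's added effect at time t: M(a_t, b_t) − M(a_t, 0). The second term needs a pyrethroid-only net of the same age.

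DuraNet is the natural stand-in. Under Study arms it has the same polymer, denier, mesh and fabric weight, with 5.8 against 6.0 g/kg alpha-cypermethrin, a difference of 0.2/6.0 = 3.3%. No DuraNet result is defined for these tunnel tests.

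**Step 4. How far the rule can move the pass rate.** Let pm be the proportion passing on mortality and q the share of mortality failures that pass on inhibition. Both are assumptions, since the article gives neither. The pass rate under mortality or inhibition is pm + (1 − pm) × q.

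| pm | q = 0.25 | q = 0.50 | q = 0.75 |
|---|---|---|---|
| 30% | 47.5% | 65.0% | 82.5% |
| 50% | 62.5% | 75.0% | 87.5% |
| 70% | 77.5% | 85.0% | 92.5% |

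For example, 0.50 + 0.50 × 0.25 = 0.625. At pm = 50% the shift is 12.5 to 37.5 points.

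**Step 5. If DuraNet is in fact tested.** Assume mortality pass rates of 20% (DuraNet) and 60% (DuraNet Plus), 30 nets per type, a two-sided 5% test, and the same q in both types. With p̄ the mean of the two rates:

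Power = Φ{[|p2 − p1| − 1.96 √(2p̄(1 − p̄)/n)] / √[(p1(1 − p1) + p2(1 − p2))/n]}

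- Mortality only: (0.40 − 1.96 × 0.1265)/0.1155 = 1.32, power 91%.
- Mortality or inhibition: 65%, 39% and 19% for q = 0.25, 0.50 and 0.75.

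So the rule would matter for a between-type test as well.

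**The case against.** The best defence is that this is loose drafting around a sound plan. The abstract merges the criteria for two actives into one parenthesis, and knockdown plainly belongs to the cone test. The analysis sentence gives no threshold and may simply summarise both assays. The resistant-strain tunnels draw on nets withdrawn for bioassays without restricting type in that phrase, and the analysis section speaks of 30 nets of each product type. Chemical analysis measures both actives at 0, 12, 24 and 36 months on pieces adjacent to the bioassay pieces, and the susceptible-strain tests track alpha-cypermethrin activity, so a drop in the pyrethroid would be visible. The hut trials compare both aged net types with resistant mosquitoes.

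Much of this stands, and it rules out three stronger readings that a reader might infer:

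- *The chi-squared test and the PBO effect cannot be delivered at all.* Not supported. The alpha-cypermethrin test covers both types under one rule, and the huts give a between-type contrast at 12, 24 and 36 months.
- *There are three conflicting thresholds.* Not supported. There is one explicit threshold conflict, between the abstract and the bioassay section. The analysis section misdescribes the assay basis but sets no third threshold.
- *DuraNet is certainly left out of the resistant-strain tunnels.* Not stated. It is inferred from the stated purpose, outcome and reference, which name only DuraNet Plus.

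The defence does not remove the mismatch. If DuraNet is run, its PBO outcome and reference are undefined. If it is not, the between-type PBO test has no second group. Chemical content is not biological effect. The huts use one wild population in Benin and give no net-level pass rate per site against the laboratory strains.

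**Conclusion.** The concern holds for the laboratory PBO endpoint only. Its pass rule differs between the abstract and the bioassay section. The analysis section assigns it a combined cone-and-tunnel basis and a between-type test that the bioassay section does not support. As defined, the assay shows whole-product activity against a resistant strain, so by itself it does not deliver the added PBO effect claimed in the Discussion.

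The number of nets that would change class cannot be known from the article. The 12.5 to 37.5 point shift rests on an assumed 50% mortality pass rate and an assumed 25% to 75% of failures passing on inhibition. The text conflicts do not depend on those assumptions.

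**What to change.** 1. **One criterion.** Use the bioassay section's rule, at least 80% resistant-strain mortality in the tunnel, for PBO in the abstract, the bioassay section and the analysis section. Keep the combined cone-and-tunnel basis for alpha-cypermethrin only.
2. **One analysis.** Limit the laboratory PBO analysis to DuraNet Plus, aged against new and over time, and delete the between-type PBO chi-squared test. Describe the result as whole-product activity, read alongside the measured content of both actives. Leave the DuraNet Plus versus DuraNet contrast to the hut trials, and reword the Discussion sentence to match.
3. **If DuraNet pieces are in fact run in the same resistant-strain rounds,** say so and define the PBO effect as the between-type mortality difference within a round.

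Items 1 and 2 cost only wording, and the downside is a narrower laboratory claim about PBO. Newly adding DuraNet would be a different matter: up to 110 further overnight tunnel tests per site, 330 over three sites, each with an animal bait. A single new DuraNet per round would be cheaper but gives only M(a_0, 0), so it would not separate PBO loss from alpha-cypermethrin loss in aged nets. The article's status section reports bioassays complete only to 6 months, and the PBO tunnels start at 12, so on that account the rule could be settled before any PBO result.

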#### Experimental hut trials

To further assess the entomological superiority of DuraNet® Plus over DuraNet®, experimental hut trials will be performed with field collected ITNs at 12-, 24- and 36-months post ITN distribution from each country at the Cove experimental hut station in Benin against wild free-flying pyrethroid-resistant *Anopheles gambiae* sl. Fifty-four (54) DuraNet® Plus and 54 DuraNet® nets from all three countries will be tested together in experimental huts at each annual timepoint. Comparison will be made with new unused nets of each type. The hut trials will consist of the following 9 treatments:Untreated net – 6 replicatesDuraNet® (new unused) – 6 replicatesDuraNet® Plus (new unused) – 6 replicatesDuraNet® Benin (12-, 24- or 36-months field net) – 54 replicatesDuraNet® Cameroon (12-, 24- or 36-months field net) – 54 replicatesDuraNet® Tanzania (12-, 24- or 36-months field net) – 54 replicatesDuraNet® Plus Benin (12-, 24- or 36-months field net) – 54 replicatesDuraNet® Plus Cameroon (12-, 24- or 36-months field net) – 54 replicatesDuraNet® Plus Tanzania (12-, 24- or 36-months field net) – 54 replicates

Each trial will last 9 weeks and will involve 9 consenting human volunteers sleeping in huts from dusk to dawn 6 days of each week of the trial. To allow assessment of blood-feeding inhibition, all unused nets will be given 6 holes each measuring 4cmx4cm in accordance with WHO guidelines [9]. Treatments will be rotated each week using a randomised Latin Square Design while sleepers will be rotated daily to control for hut position effect and sleeper attractiveness to mosquitoes respectively. On the 7^th^ day of each week, huts will be cleaned and aired in preparation for the next rotation cycle. The trials will run for a total of 54 nights and replicate nets collected from the field will be rotated between huts on successive nights (one net per night). The efficacy of each ITN hut treatment at each timepoint will be measured in terms of the proportion of mosquitoes dead after 24 h, proportion exiting into the veranda trap and the reduction in blood-feeding relative to the control untreated nets. The intensity of resistance to pyrethroids in the vector population at the hut site and the involvement of mixed function oxidases in pyrethroid resistance will be assessed during each experimental hut trial following standard WHO susceptibility bioassay guidelines [15].

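### In the hut trials net age coincides with trial year, and the over-time mortality model does not say that it uses the new-net arms that could separate the two

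*Protocol article*

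**What the plan says.** The section Experimental hut trials in the Protocol article describes a trial at each of 12, 24 and 36 months, all at the Covè station against wild pyrethroid-resistant mosquitoes. Field nets from the three countries "will be tested together in experimental huts at each annual timepoint". Each trial has nine treatments: an untreated net, new DuraNet, new DuraNet Plus, and field nets of each product from each country. On the new nets the section says: "Comparison will be made with new unused nets of each type".

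The same section plans, in each trial, to assess "The intensity of resistance to pyrethroids in the vector population at the hut site" and the part that oxidases play in it.

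On holes it says "all unused nets will be given 6 holes each measuring 4cmx4cm in accordance with WHO guidelines", with the purpose "To allow assessment of blood-feeding inhibition". No standard holes are stated for field nets. One hut outcome is "the reduction in blood-feeding relative to the control untreated nets".

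Data management and analysis compares hut outcomes at each time point by mixed-effects logistic regression. It then adds a model to determine "whether there is a significant change in improved mosquito mortality achieved DuraNet® Plus compared to DuraNet® over time and between the three countries". That sentence mentions neither the new-net arms, nor a field-versus-new term, nor the resistance data.

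**The concern.** Each net age is seen in one trial only, and each trial meets whatever mosquito population is at the station that year. If that population becomes more or less responsive to PBO, the DuraNet Plus advantage over DuraNet changes even when the nets have not. A comparison of the aged-net contrast across trials would attribute that change to ageing. The error can go either way: a false loss of PBO benefit, or a real loss hidden by an opposite shift. The Discussion relies on this comparison, since it says the design allows nets of different ages to be compared directly.

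A separate and smaller point concerns blood-feeding. Field nets carry whatever damage they acquired in use, while the new nets and the untreated control carry a fixed hole area. A difference in feeding between a field net and either of these therefore reflects fabric as well as insecticide.

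**Working it through.** **Figures in the plan.** 9 weeks × 6 nights = 54 nights per trial, as stated. 54 hut nets × 3 annual trials = 162 per product and site, as in Table 2. Nine treatments × 54 nights = 486 hut-nights per trial. New nets of each type have 6 replicates, so 6 nets × 9 nights = 54 hut-nights. Each field arm has 54 nets for one night each, so a product pooled over three countries has 3 × 54 = 162 hut-nights per trial. Hole area on an unused net is 6 × 4 cm × 4 cm = 96 cm².

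**What cancels.** Write the log odds of death in trial t as a(t) for DuraNet and a(t) + b(t) for DuraNet Plus. The planned contrast is b(t) and its change is b(2) − b(1). Any change in a(t) drops out. A change in b(t) stays, whether it comes from the nets or from the mosquitoes. The anchored contrast is b(field, t) − b(new, t). New nets have not aged, so a population change in b that acts alike on new and field nets drops out and ageing remains.

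**Simulated size.** The documents give no hut mortality, mosquito count or between-year shift, so all inputs here are assumptions: 10 mosquitoes per hut-night, hut-night SD 0.7 on the logit scale, new DuraNet mortality about 27%, PBO log odds ratio 1.0, 162 field and 54 new-net hut-nights per product per trial, two trials compared, two-sided 5% test, 4,000 runs. The last two columns give the share of runs declaring a change.

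| Scenario | Planned contrast | Anchored contrast |
|---|---|---|
| No shift, no ageing | 5.1% | 5.5% |
| Shift of −0.5 common to both products | 5.0% | 5.1% |
| PBO response shifts −0.2, no ageing | 24% | 5.1% |
| PBO response shifts −0.4, no ageing | 70% | 5.1% |
| Ageing loss 0.4 hidden by a +0.4 shift | 4.5% | 26% |
| Ageing loss 0.4, no shift | 70% | 25% |

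**Cost in precision.** With variance proportional to 1/hut-nights, the SE ratio of anchored to planned contrast is √(1 + n_field/n_new). For one country it is √(1 + 54/54) = 1.41. Pooled, it is √(1 + 162/54) = 2. The simulation agrees: 0.145 against 0.286. This takes the hut-night as the unit of information. If individual nets differ, having only 6 new nets would widen the anchored interval further.

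**Holes.** The section Follow-up for ITN fabric integrity scores holes on cohort 1. Destructively sampled nets are examined only if cohort 1 falls short of 250. Hole area on hut nets is therefore not routinely recorded.

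**The case against.** The strongest reply is that the anchor is already in the design and that comparison with new nets is stated. The analysis sentence names a question rather than model terms, and a condensed article may leave those terms to a fuller document. This stands to a large extent: nothing in the text excludes the new nets. The gap is that the one stated over-time target is a Plus-versus-DuraNet change with no reference to them.

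A reader might infer that any year-to-year change in the mosquitoes biases the result. It does not, since a shift common to both products cancels. The choice of scale matters too. If mortality went from 30% and 60% to 20% and 40%, the odds ratio would fall from (0.6/0.4)/(0.3/0.7) = 3.50 to (0.4/0.6)/(0.2/0.8) = 2.67, while the risk ratio stayed at 2.0. Nor does re-measuring resistance show that the sponsor expects it to change.

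A reader might also infer that the hole rule confounds the DuraNet Plus comparison. It does not enter that contrast, because both field arms have the same age and natural wear. Natural damage is part of what a durability study measures, so leaving field nets without cut holes is not an error. Adjusting feeding for hole area would condition on a consequence of ageing and answer a different question.

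Finally, PBO durability is also assessed by tunnel tests with characterised resistant strains and by chemical content. The hut result is not the only evidence. It is, however, the one against wild mosquitoes, and the Discussion links it to likely performance against clinical malaria.

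**Conclusion.** The concern holds in a limited form. Net age and trial year coincide, and the stated over-time model does not say how they are to be separated. A between-year change in the population's response to PBO could therefore be mistaken for loss or retention of PBO benefit. The 24% and 70% false-change rates are illustrations under assumed inputs, not predictions. Anchoring rests on the assumption that a population shift acts alike on new and field nets on the log-odds scale. It also brings the hole difference into the mortality contrast, where it largely cancels if it acts alike on both products.

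The documents do not support saying that the hut trials are confounded in general. Same-age comparisons of the two products within a trial are unaffected, and between-country comparisons within one trial meet the same mosquitoes. They also do not support replacing the planned contrast: with no population shift, the anchored test's power for a loss of 0.4 falls from 70% to 25% under the same assumptions.

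On feeding, comparisons of field nets with new nets or with the untreated control measure total net performance. They should not be read as insecticide durability.

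**What to change.** 1. Keep the planned field-net contrast. Add the new-net arms of each trial to the over-time mortality model, as a product × field/new × trial interaction.
2. Report the anchored contrast beside the unanchored one, with intervals, and show the new-net results and resistance findings for each trial. Three trial-level resistance values are context and too few for adjustment.
3. Attribute a change over time to net ageing only if the anchored result is consistent with it. Because its interval is wide, the anchored result should be judged on direction and size and need not be significant alone.
4. Score the holes of each field net on the existing frame before hut use, and report hole area beside feeding inhibition. Describe that outcome as total net performance. A hole-adjusted feeding model is at most a sensitivity analysis.

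The cost is model wording and hole scoring of 6 × 54 = 324 field nets per trial, with no new arm. The statistical price is the wider anchored interval, which is why that contrast accompanies the planned one. The modelling change can use new-net data from trials already run; hole scoring before use can only apply to nets not yet tested.
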